### Objectives

A feasibility design was deemed necessary to determine whether a full-scale randomised controlled trial (RCT) is feasible, by considering numbers meeting eligibility criteria, rates of recruitment and retention postrandomisation, floor/ceiling effects that might affect sensitivity to change; as well as by identifying any intervention-specific issues, particularly occurrence of adverse events and timing burden. The following aims will be addressed in this feasibility RCT:Objective 1: to estimate rates of recruitment and retention.Objective 2: to estimate willingness to be randomised.Objective 3: to explore the level of adherence to the intervention (intervention arm only).Objective 4: to estimate the standard deviation (SD) of fatigue in this patient population in order to compute a more robust estimate of the sample size required for an efficacy trial.Objective 5: to preliminary assess the psychometric properties of the self-report instruments used.Objective 6: to explore the potential benefits of the intervention at reducing fatigue severity and fatigue-related functional impairment as compared with the waiting-list control.Objective 7: to explore the potential benefits of the intervention at reducing depression and anxiety and improving sleep quality as compared with the waiting-list control.Objective 8: to examine change in fatigue-related cognitions and behaviours, and whether their effect differs between the intervention and control arm.Objective 9: to qualitatively explore patient perceptions of the acceptability and usefulness of the intervention and identify areas of improvement for a future full-scale trial.Objective 10: to explore any intervention-specific issues, particularly setting, mode of delivery of the intervention and acceptable number of sessions/chapters.

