### Randomisation, allocation concealment and blinding

Participants will be randomised in a 1:1 ratio to receive either the cognitive-behavioural therapy for renal fatigue (BReF) intervention or to the waiting-list control. Participants will be randomised at the individual level. Randomisation will be stratified by centre and randomly varying block sizes will be used to maintain balance of numbers in each arm across the period of recruitment while maintaining allocation concealment. King’s College London’s independent randomisation service will be used. Because the randomisation sequence is automated in real time, the allocation sequence is concealed from researchers. The trial coordinator will receive an automated email with the outcome of the randomisation procedure. The nature of the trial is such that blinding of participants cannot be achieved. Follow-up outcomes will be completed independently by participants by post or online. If baseline or follow-up questionnaires are not completed, then participants will receive reminder emails or phone calls and an assistance-based visit at the dialysis unit, by an independent researcher, who has not been involved in the intervention delivery. The statistician will remain blinded to treatment allocation.

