### Secondary self-reported patient outcomes

Self-reported patient outcomes will also be collected at baseline (T0) and 3 months postrandomisation (T1) via post or online. The assessment schedule completed by patients is summarised in table 3 and the self-report instruments used are described below.

**Table 3 T3:** Schedule of assessments

Assessment	Time		
	Screening	Baseline (T0)	Postintervention (T1)
CFQ	x	x	x
WSAS		x	x
PHQ-9		x	x
GAD-7		x	x
PSQI		x	x
BIPQ		x	x
CBSQ		x	x
SHI		x	x
IPAQ-short		x	x
CCI		x	
Sociodemographic characteristics	x	x	
Clinical characteristics	x	x	
Biochemical outcomes		x	x
Self-reported adverse events			x
Self-reported treatments for distress or fatigue during study			x
Qualitative interviews			x

BIPQ, Brief Illness Perceptions Questionnaire; CBSQ, Cognitive and Behavioural Responses to Symptoms Questionnaire; CCI, Charlson Comorbidity Index; CFQ, Chalder Fatigue Questionnaire; GAD-7, Generalised Anxiety Disorder-7; IPAQ-short, International Physical Activity Questionnaire -short form; PHQ-9, Patient Health Questionnaire-9; PSQI, Pittsburgh Sleep Quality Index; SHI, Sleep Hygiene Index; WSAS, Work and Social Adjustment Scale.

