### Adverse events

Information about occurrence of serious adverse events since the start of the study will be collected by self-report postintervention, according to good clinical practice guidelines. Adverse events will be flagged up to the trial management team and participants will be contacted to further assess the adverse event and its relationship to the study.

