### Demographic, social situational and clinical characteristics

At baseline, sociodemographic characteristics, including: gender, age, ethnicity, marital status, employment status, education, living arrangements, exercise, smoking status and alcohol consumption; and clinical characteristics, including: dialysis vintage and receipt of anaemia treatments will be collected via self-report.

Extra renal comorbidity will be assessed at baseline by consultant nephrologists using the Charlson Comorbidity Index (CCI).^77^ This instrument is a weighted index that takes into account the number and the seriousness of comorbid diseases and can be adjusted for age. The method of classifying comorbidity provides a simple, readily applicable and valid method of estimating risk of death from comorbid disease for use in longitudinal studies.^77^ The CCI has been previously used with and determined suitable for patients on dialysis.^78 79^

Clinical information, including: dialysis adequacy (urea reduction ratio), interdialytic weight gain, haemoglobin, ferritin, serum albumin, creatinine, urea, phosphate, potassium, calcium, C reactive protein and primary renal diagnosis will be extracted from patients’ medical notes at baseline (T0) and postintervention (T1).

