### Ethics

The trial is co-sponsored by King’s College London and King’s College Hospital NHS Foundation Trust. Patient consent will be obtained. The Chief Investigator (CI) and all members of the research team will preserve the confidentiality of participants taking part in the study and will work in accordance with the Caldicott Principles, Data Protection Act 1998, NHS Code of Confidentiality and any relevant NHS Trust organisational policies. All serious adverse events related to the study will be reported to the study sponsor, ethics committee and relevant NHS R&D departments. Authorisation will be sought from the study sponsor for any future substantial and non-substantial amendments arising during the course of the study, prior to submission to the HRA. The study may be subject to inspection and audit by King’s College London under their remit as sponsor and other regulatory bodies to ensure adherence to GCP and the NHS Research Governance Framework for Health and Social Care (second edition).

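### The only stated source for serious adverse events is self-report at 3 months, so events in participants who do not return that questionnaire are not captured, although medical notes are already read then

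*Protocol article*

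**What the plan says.** The *Adverse events* section gives both source and timing: "Information about occurrence of serious adverse events since the start of the study will be collected by self-report postintervention". Once an event has been flagged, the next step also goes through the patient: "participants will be contacted to further assess the adverse event and its relationship to the study". Table 3, the schedule of assessments, has one matching row, "Self-reported adverse events", ticked only in the T1 column.

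The section on randomisation and blinding describes how T1 data arrive: "Follow-up outcomes will be completed independently by participants by post or online". If a questionnaire is outstanding, "participants will receive reminder emails or phone calls and an assistance-based visit at the dialysis unit".

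The section on demographic and clinical characteristics plans an extraction from the medical notes at baseline and again at T1. Its listed items are dialysis adequacy, interdialytic weight gain, laboratory values and primary renal diagnosis. Deaths, admissions and SAEs are not on the list.

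Two other places give the SAE data a purpose. *Objectives* names, among the intervention-specific issues that the design should identify, "particularly occurrence of adverse events and timing burden". *Ethics* sets a duty: "All serious adverse events related to the study will be reported to the study sponsor, ethics committee and relevant NHS R&D departments".

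**The concern.** A participant must be alive, well enough and willing to complete T1 for an event to be recorded by the stated method. In-centre haemodialysis patients who have had a serious event may be less able to do so, in which case the missing data depend on the outcome being counted. The SAE count would then tend to be too low.

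Two uses of the data are at stake. The first is the feasibility question of how often adverse events occur, which will inform a decision about a full trial. The second is the onward reporting of related SAEs, which can only work for events that the team knows about. The article specifies the source and the timing itself, in the text and in the schedule, and the two agree. So this is a point about a stated method, not about detail left to a fuller document.

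**Working it through.** **Inputs from the article**
- Planned sample: 40, randomised 1:1 (*Abstract*, *Sample size*).
- Assumed retention: 80% (*Sample size*).
- One follow-up, at 3 months (*Design*).
- SAE source: self-report at T1 (*Adverse events*, Table 3).

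**Inputs not in the article (assumptions)**
- The ratio *m* of SAE risk in non-responders to that in responders.
- The 3-month risk of death.

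**Step 1: the plan's own figure.** No SAE figure is stated. The retention input can be checked: 32 of 40 gives an exact 95% interval of 64.4% to 91.0%, a half-width of 13.3 percentage points. That agrees with the 13% margin in *Sample size*, which the article describes as a margin for the consent rate.

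**Step 2: participants with no self-reported SAE data.** 40 × (1 − 0.80) = 8. This is an upper figure at that retention, because someone counted as lost might still be reached by a call or an assisted visit.

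**Step 3: share of SAEs unseen.** With 80% responding at risk *r* and 20% not responding at risk *m* × *r*, the share is 0.20*m* / (0.80 + 0.20*m*). The risk *r* cancels, so no absolute SAE rate is needed.
- *m* = 1: 0.20 / 1.00 = 20%.
- *m* = 2: 0.40 / 1.20 = 33%.

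**Step 4: could a death plausibly occur in the trial?** For a 3-month risk *p*, the chance of at least one death among 40 is 1 − (1 − *p*)^40.

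| Assumed 3-month risk | Expected deaths | Chance of at least one |
|---|---|---|
| 2% | 0.8 | 55% |
| 4% | 1.6 | 80% |
| 8% | 3.2 | 96% |

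Over this assumed range a death is more likely than not, and it could not enter through a self-report item.

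**Step 5: is there another route in the text?**
- Reasons for drop-out are recorded and reported (*Analysis plan*). A known death could appear there, but as participant flow and not as an SAE. A hospital admission in someone who simply does not reply would not appear.
- Reminders and assisted visits raise the response. They do not create a record for those still not reached.
- Notes are read at T1, but events are not among the listed items.

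None of these is designated as a source of SAEs.

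**Step 6: after the change.** With the notes as a source for all randomised participants, the number without SAE information moves from up to 8 of 40 towards 0 of 40, limited by access to the notes.

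**The case against.** The best case for the plan has four parts.

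*Silence is not exclusion.* This is a condensed article. It ties adverse-event collection to good clinical practice, and *Ethics* commits to reporting related SAEs. Ad hoc logging by staff and reporting timelines usually sit in the full protocol. That is fair, and the point is limited to the only source that the article states. It makes no claim about reporting deadlines.

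*The team would probably hear of a death.* A reader might infer that deaths cannot be counted at all. The article does not support that. Drop-out reasons are recorded, outstanding questionnaires are chased, control participants are telephoned, and these patients attend a dialysis unit regularly. What stands is narrower: a death learned of in this way has no defined path into the SAE count, and admissions in persistent non-responders have no path at all.

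*The arms are treated alike.* A reader might infer from the therapist sessions that the stated method ascertains the two arms differently. It does not. The question and the time point are the same for both, and an assisted visit is made by a researcher not involved in delivery. The imbalance would arise only if events heard in therapy sessions were added informally. The remedy has to guard against that.

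*The size is uncertain.* The 80% is a planning assumption, and the article gives no SAE rate. A much larger share missed can be produced by assuming a high event rate in non-responders, but nothing in the article supports a particular value. Only the 20% at equal risk, and the direction of change if non-responders are at higher risk, can be stated with any firmness.

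Adverse events are also not among the ten numbered objectives or the primary feasibility outcomes. That limits how much rests on this point.

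**Conclusion.** The point holds in a limited form. The stated route loses SAEs, including admissions, in participants who do not return T1, and it leaves a death to appear only as a reason for drop-out. At the plan's 80% retention this affects up to about 8 of 40 participants. About 20% of SAEs would be unseen if risk is equal in responders and non-responders, and about 33% if non-responders have twice the risk. The first figure rests on the plan's retention assumption. The second adds an assumption that the article neither gives nor rules out.

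This is a moderate weakness with a cheap remedy. It does not alter recruitment, retention, adherence or the planned effect estimates. It does weaken the answer to a question that the article gives as a reason for the feasibility design.

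**What to change.** 1. Add deaths, hospital admissions and other SAEs to the medical-notes extraction already planned at T1. Do this for every randomised participant, in both arms, whether or not the questionnaire is returned, and over the same look-back period as the self-report item.
2. Keep self-report as a supplement, for events that the notes may not hold.
3. Report SAEs by arm with all randomised participants as the denominator, and state how many had no information from either source.
4. Identify separately any event learned of through therapist contact. That route exists mainly in the intervention arm, and mixing it in unmarked would create a difference in detection that the present method does not have.
5. Amend the *Adverse events* section and Table 3 to match.

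The cost is a few extra fields in an existing extraction for 40 patients, plus the wording. No new visits or staff are needed.

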### Other treatments

Participants will be asked whether they have received any pharmacological, psychological or exercise-based treatment for depression and/or anxiety and/or fatigue in addition to BReF since starting the study.

### Demographic, social situational and clinical characteristics

At baseline, sociodemographic characteristics, including: gender, age, ethnicity, marital status, employment status, education, living arrangements, exercise, smoking status and alcohol consumption; and clinical characteristics, including: dialysis vintage and receipt of anaemia treatments will be collected via self-report.

Extra renal comorbidity will be assessed at baseline by consultant nephrologists using the Charlson Comorbidity Index (CCI).^77^ This instrument is a weighted index that takes into account the number and the seriousness of comorbid diseases and can be adjusted for age. The method of classifying comorbidity provides a simple, readily applicable and valid method of estimating risk of death from comorbid disease for use in longitudinal studies.^77^ The CCI has been previously used with and determined suitable for patients on dialysis.^78 79^

Clinical information, including: dialysis adequacy (urea reduction ratio), interdialytic weight gain, haemoglobin, ferritin, serum albumin, creatinine, urea, phosphate, potassium, calcium, C reactive protein and primary renal diagnosis will be extracted from patients’ medical notes at baseline (T0) and postintervention (T1).

### Qualitative interviews

To complement the quantitative process evaluation and further explore the acceptability of the intervention, in line with current MRC process evaluation guidelines,^80^ qualitative interviews will be conducted with a subgroup of participants from the intervention group at 3 months postrandomisation (T1). The interviews will be semistructured and will be conducted over the phone or face-to-face, in a private environment. The interviews will be conducted by an independent researcher, who has not been involved in the intervention delivery. The main aim of the interviews will be to gather participants’ experiences of the intervention, to identify areas of improvement. Purposive maximum variation sampling will be employed to ensure variability of the sample across a range of sociodemographic and clinical characteristics,^81^ in particular: age, gender, ethnicity, dialysis vintage, degree of adherence to the intervention, degree of improvements in outcomes following the intervention. A minimum of 10 interviews will be conducted, until data saturation is reached, meaning the point where no new data is obtained with every new interview.^82^

### Sample size

The renal service of King’s College Hospital has approximately 550 patients on HD and Lister Hospital has approximately 510 patients on HD, in which we expect to be able to approach 636 (60%) during the recruitment period. Past psychological research in patients on dialysis, conducted by the team, suggest consent rates between 50% and 70%, assuming a more conservative uptake of 40%, 254 patients are expected to be screened, with approximately 30% (n=76) expected to meet the inclusion criteria, including around half reporting clinical levels of fatigue.^59^ Assuming 50% of those eligible will consent to be randomised (n=38), a sample size of 40 participants would allow us to estimate the true population consent rate with a 11% margin of error (95% binomial exact confidence level) for those meeting eligibility criteria. In line with recommended sample sizes of pilot feasibility trials,^83–85^ 40 patients is deemed sufficient to explore feasibility, acceptability and potentially efficacy of the intervention, assuming retention rates of 80%, the true population consent rate will be with a margin of error of 13% (95% binomial exact CI), an acceptable level of error, based on the time, budget and workforce constraints, as FP will act as both the trial coordinator and therapist.

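### The 13% margin in the sample size section is a retention margin labelled as a consent-rate margin, and the 11% consent margin needs a denominator the article does not state

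*Protocol article*

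**What the plan says.** All the figures are in the Sample size section of the protocol article. The recruitment funnel starts from about 550 and 510 haemodialysis patients at the two sites: "we expect to be able to approach 636 (60%) during the recruitment period". It applies 40% uptake to that number and continues: "254 patients are expected to be screened, with approximately 30% (n=76) expected to meet the inclusion criteria". The next step is: "Assuming 50% of those eligible will consent to be randomised (n=38").

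Two precision statements follow. The first is that "a sample size of 40 participants would allow us to estimate the true population consent rate with a 11% margin of error", qualified by the words "95% binomial exact confidence level) for those meeting eligibility criteria". The second, which the section treats as a tolerable level of error, reads: "assuming retention rates of 80%, the true population consent rate will be with a margin of error of 13% (95% binomial exact CI").

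The Objectives section lists both quantities as things to be estimated: "Objective 1: to estimate rates of recruitment and retention". The section on primary feasibility outcomes also names recruitment and retention rates.

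**The concern.** A consent rate and a retention rate have different denominators. The consent rate is measured on eligible patients who are asked to be randomised. The retention rate is measured on those who were randomised. Drop-out after randomisation cannot alter how precisely the consent rate is known, so a consent-rate margin that depends on 80% retention cannot be right as labelled.

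Read literally, the paragraph gives one quantity two margins, 11% and 13%, and gives the other no margin. In addition, the 11% is tied to 40 participants and to eligible patients, but the number of eligible patients behind it is not given, and the number printed just before it does not reproduce it by the stated method.

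At stake is the clarity of the precision argument for n=40. A reader planning the later efficacy trial would take from it the wrong precision for one feasibility rate and none for the other.

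**Working it through.** **Inputs, all from the Sample size section:** 550 + 510 = 1,060 patients; 60% approached; 40% uptake; 30% eligible; 50% of those eligible consenting; 40 randomised; 80% retained; exact binomial intervals at 95%.

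**Funnel.** 1,060 × 0.60 = 636. 636 × 0.40 = 254.4, printed as 254. 254 × 0.30 = 76.2, printed as 76. 76 × 0.50 = 38. The funnel reproduces.

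**Method.** The exact (Clopper-Pearson) 95% interval for x successes in n has lower limit equal to the 2.5% quantile of Beta(x, n − x + 1) and upper limit equal to the 97.5% quantile of Beta(x + 1, n − x). The margin is taken as (upper − lower)/2.

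**The 11%.** If 40 are the patients who consent, at 50% consent, the number eligible is 40/0.50 = 80.

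| Consenting/eligible | Exact 95% CI | Exact margin | Wald margin |
|---|---|---|---|
| 40/80 (implied by n=40) | 38.6% to 61.4% | ±11.4 | ±11.0 |
| 38/76 (printed funnel) | 38.3% to 61.7% | ±11.7 | ±11.2 |

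The stated 11% is reproduced with 80 eligible. With the 76 that the section prints, the stated exact method gives 11.7, which rounds to 12%.

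**The 13%.** 80% of 40 is 32. Exact 32/40 gives 64.35% to 90.95%. The half-width is (90.95 − 64.35)/2 = 13.3, which rounds to the stated 13%. The interval is not symmetric: 80 − 64.35 = 15.65 points below and 90.95 − 80 = 10.95 points above.

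**Could 13% still be a consent-rate margin?** At 50% consent, an exact margin that rounds to 13% arises with about 61 eligible (±13.1) or 64 eligible (±12.8). Those are 80% of 76 (60.8) and 80% of 80 (64). Reaching them means removing a fifth of the eligible patients from the consent denominator because of later drop-out. That has no rationale, since a patient who consents and later drops out has still consented. On this route too, the sentence is wrong.

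**The case against.** The best defence is that both numbers are correct for some quantity, so this is a labelling slip and not an arithmetic error. That is right, and it limits the point to minor. The section also rests n=40 on recommended sizes for pilot trials and on time, budget and workforce, so the sample size does not depend on these margins alone.

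A reader might infer something stronger about the 11%: that 40 observations at 50% give an exact margin of ±16.2, so 11% is impossible. The text does not support this. It treats the 40 as those who consent, assumes half of eligible patients do so, and refers the margin to those meeting the eligibility criteria. The implied denominator is 80, for which 11% is correct. What remains is that 80 is never stated and differs from the printed 76. The difference in margin is only 0.3 points, and the funnel's inputs are themselves approximate.

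A reader might also infer that quoting 13 points when the lower limit lies 15.65 points below 80% biases a decision to proceed. The article states no retention threshold. It describes a broad judgement covering recruitment, retention, measures and intervention issues, so no stated decision turns on this. Quoting a half-width as a margin is common shorthand. Likewise, the article claims no precision by arm or for adherence, so the lack of such figures is not an error.

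None of this rescues the label on the 13%.

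**Conclusion.** Wrong as written; minor. The 13% agrees with the exact half-width for 80% retention among 40 randomised (13.3 points; interval 64% to 91%) and is printed as consent-rate precision. The 11% is sound for an unstated 80 eligible patients (±11.4) but becomes 12% (±11.7) on the section's own 76.

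This rests on the plan's assumed rates of 50% consent and 80% retention, on exact 95% intervals as the plan specifies, and on reading the 13% as retention precision, which is an inference from the match. The mislabelling does not depend on that last inference, because no reading makes post-randomisation retention a determinant of consent-rate precision.

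**What to change.** Replace the two precision statements with text such as:

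> With about 76 eligible patients, a 50% consent rate is estimated to within ±12 points (exact 95% CI 38% to 62%; ±11 if 80 are eligible). With 40 randomised, an 80% retention rate has an exact 95% CI of 64% to 91%.

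Giving both 76 and 80 shows openly that the funnel yields 38 consenting patients while the target is 40. Giving retention as an interval avoids suggesting that it is symmetric. The cost is a text correction only: n=40, the design and the analysis stay as they are, and the stated consent precision on the printed funnel becomes one point wider.
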